##### Sample size and feasibility

We will recruit a minimum of four general practices to the study. Based on data from a previous study [48], it is anticipated that each practice will identify 104 potentially eligible patients with a diagnosis of COPD with 50% participation and 52 patients are likely to consent to take part in the study. It is estimated that the four practices will identify a total of 1060 patients who are at risk of COPD but without a current diagnosis. Of these, 17% (180) will attend for spirometry and assessment and 18% [33] will receive a new diagnosis of COPD [12].

## Statistical analysis

Data will be analysed using SPSS statistical software with a two-sided significance level set to 0.05. Descriptive analyses will be used to evaluate the process outcomes. Paired *t* test for significance will be performed to compare patient responses in the baseline and 3-month follow-up questionnaires. Interviews with the participating GPs, PNs and physiotherapists will be undertaken and will be digitally recorded, transcribed verbatim and analysed thematically. The researchers will code the data using NVivo. We will use the Theoretical Domains Framework to guide the coding and analysis of the health professional transcripts [49]. The patient transcripts will be coded thematically and triangulated with the health professional data.

## Discussion

We anticipate that the GP and physiotherapist partnership will be feasible and will improve the diagnosis and management of COPD in primary care in the participating practices. Current evidence suggests that spirometry use in primary care is low [8–10] and misinterpretation of spirometry results and misdiagnosis of COPD is high [12–14]. Lack of confidence expressed by GPs and PNs at interpreting spirometry [11] could contribute to this, and there is also recent evidence emerging regarding people with COPD fluctuating in and out of diagnostic status. One study [50] found that up to one-third of symptomatic ex-smokers with baseline obstruction on diagnostic spirometry had shifted to non-obstructed when routinely re-tested after 1 or 2 years. This highlights the difficulties surrounding diagnosis and the importance of follow-up testing. We hope that including physiotherapists with expertise in the performance and interpretation of spirometry will improve the accuracy of diagnosis as well as identify new cases of COPD in those deemed ‘at risk’ of developing COPD. Studies have also reported suboptimal referral by GPs to pulmonary rehabilitation and poor patient attendance and completion rates [20–23, 51, 52] which is one of the most effective treatments for COPD. More effective management of COPD in primary care and increased uptake of pulmonary rehabilitation could lead to improvements in the quality of care and health outcomes for people with COPD.

In Australia, physiotherapists are highly trained in the management of cardiorespiratory problems in secondary care. Australian physiotherapists are crucial to the delivery of exercise training programmes including PR, as well as providing therapies to increase sputum production, reduce work of breathing and improve overall ventilation. Respiratory physiotherapists in Europe also undertake extensive training in these areas as well as conducting and interpreting pulmonary function testing [53]. Physiotherapy services, as a first point of contact, have been shown to be effective in patients with musculoskeletal skeletal complaints [32] and a viable alternative to GP care. It was suggested in another study [33] that up to 85% of musculoskeletal complaints in a general practice in Sweden could be managed solely by the physiotherapist. Currently, there is no published research on the effectiveness of physiotherapists providing cardiorespiratory interventions in partnership with GPs and this model of care needs further investigation within an Australian landscape.

The INTEGRATED study will test the efficacy of a new model of care integrating experienced cardiorespiratory physiotherapists with GPs to improve outcomes for people with COPD. Proven case-finding methods in an at-risk population will be used to identify new cases of COPD and confirm current diagnoses, as well as implement evidence-based guidelines for COPD management. This study targets COPD patients within a primary care setting where the contact with potential COPD patients with mild to moderate obstruction is greatest and where improved care has the potential for substantial health benefit. The process outcome measures that will be used in this study are based on components of evidence-based care for patients with COPD [5]. These measures will allow us to determine the integrity of the intervention and to what extent the physiotherapist was able to support the GP in delivering best practice. Other outcome measures used will enable us to measure the impact of the care provided on patient-level outcomes for example impact on health status, symptom scores, smoking status and self-reported hospital utilisation. The results from the qualitative interviews, particularly feedback obtained from participants in this study, will be used to inform and further modify the intervention for future randomised controlled trials (RCTs). A limitation to this study is that assessment measures will be performed by the treating physiotherapist and not a blinded assessor. Whilst many of the outcomes assessed in this study are self-reported which reduces the impact of bias, any future RCTs will have blinded assessors.

If this model of GP physiotherapist partnership is feasible, further research will test the effectiveness and cost-effectiveness of this model in a RCT. This model has the potential to inform models of care that better integrate physiotherapists (upskilled in cardiothoracic physiotherapy) with GPs to improve service delivery to the increasing numbers of people with COPD in Australia. Furthermore, there are several other chronic conditions such as osteoarthritis, other musculoskeletal conditions and falls that are commonly encountered in primary care with effective physiotherapy interventions. This model of care for COPD could provide a template for integrating physiotherapists more effectively into the general practice team to inform other models of care and improve outcomes for people with these chronic conditions. Currently, there is no research evidence for physiotherapists and GPs working in partnership in this way in Australia so this project will provide the first examination of this integrated care approach.

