## Study aims and hypothesis

The primary aim of the INTEGRATED study (InNovaTivE Gp-physiotheRapist pArTnErship for copD) is to determine the feasibility and acceptability of this integrated model of GP and physiotherapist partnership. The secondary aims are to (1) produce high-quality spirometry with accurate interpretation to both identify new cases of COPD and determine the stage of severity for known cases of COPD, (2) increase general practice referrals to pulmonary rehabilitation for people that meet the COPD-X guidelines criteria for referral [5], (3) increase physical activity levels in people with COPD at 3 months compared to baseline and (4) increase smoking cessation in those who are smokers at baseline.

The INTEGRATED study hypothesises that a GP and physiotherapist model of care will be a feasible and acceptable way to improve the diagnosis and management of people with COPD. This will be achieved through more accurate spirometry interpretation, at least 90% of participants who meet the COPD-X guidelines for referral to PR being referred to a programme, an increase in physical activity levels by participants at 3 months compared to baseline, and at least 50–75% of participants have attended or commenced a smoking cessation programme at 3 months after their baseline visit.

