## Methods

The INTEGRATED study is a before and after feasibility study within the ‘health services’ research domain with the aim of trialling a new model of care intended for use in a larger cluster randomised controlled trial (RCT). The protocol has followed the TIDieR (Template for Intervention Description and Replication framework) Framework. The study is being conducted in metropolitan Sydney, Australia, and commenced recruitment in October 2018 with the aim of continuing to review participants into June 2020. The research and data collection plan is summarised in Fig. 1. A minimum of four general practices will be recruited to the study from a local Primary Health Network (PHN). Physiotherapists from the rehabilitation service of the corresponding Local Health District (LHD) will run a weekly respiratory clinic at each of the participating general practices.

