### Outcome measures

The physiotherapist will collect demographic information including age, gender, body mass index, employment status, education and country of birth for all individuals who attend the respiratory clinic. Patient and process outcomes will also be collected in people with existing COPD and those with newly diagnosed COPD.

Data will be collected at baseline and at the 1-month and 3-month follow-up visits so the level of change in the outcomes following the intervention can be determined. If patients are unable to attend the appointment at 3 months with the physiotherapist, the research assistant will complete the assessment by telephone.

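### The Discussion credits an uncontrolled before-after study with testing efficacy, and self-report to the treating physiotherapist with reducing bias; the design supports neither statement

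*Protocol article*

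**What the plan says.** The Methods section states that the study "is a before and after feasibility study", intended to trial a model of care for a larger cluster randomised trial. Under Study aims and hypothesis, the primary aim "is to determine the feasibility and acceptability of this integrated model of GP and physiotherapist partnership"; higher physical activity at 3 months and more smoking cessation are secondary aims. The close of the Discussion leaves effectiveness and cost-effectiveness to a future randomised trial.

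Earlier in the Discussion the claims are larger. The study "will test the efficacy of a new model of care", and "Other outcome measures used will enable us to measure the impact of the care provided on patient-level outcomes". The same paragraph lists as a limitation that the treating physiotherapist, not a blinded assessor, performs the assessments. It then qualifies this: "Whilst many of the outcomes assessed in this study are self-reported which reduces the impact of bias". Blinded assessors are promised for future trials.

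The Statistical analysis section sets a two-sided 0.05 level, with paired t tests of questionnaire responses at baseline against 3 months. Under Outcome measures, if a patient cannot attend at 3 months, "the research assistant will complete the assessment by telephone".

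**The concern.** Two statements about what the study can show do not match its design.

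**Efficacy.** With no concurrent control, the change from baseline to 3 months combines any effect of the model with regression to the mean, season, the natural course of the disease, usual GP care and shifts in how people answer. A paired test asks whether the mean change differs from zero. It cannot say why.

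**Self-report.** The physiotherapist gives the activity counselling and smoking advice, sees the patient again at 1 month to set a goal, and at 3 months reviews that goal at the visit where the questionnaires are completed. For a self-reported outcome the participant is in effect the assessor, and this participant is unblinded and is answering the clinician who counselled them. The protocol therefore offers as a protection something that is itself a route for bias.

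A smaller point adds to this. Mode and assessor at 3 months depend on whether the patient attended, which may be related to how the patient is doing.

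At stake is the reading of the patient outcomes, including the activity aim. A significant change could be reported as an effect of the care.

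**Working it through.** **1. The statements side by side.**

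| Topic | Design sections | Discussion |
|---|---|---|
| Purpose | Feasibility and acceptability (Study aims and hypothesis) | Tests efficacy; measures impact on patients |
| Comparison | Before and after, one group (Methods); paired t test (Statistical analysis) | No control mentioned; effectiveness left to a later trial |
| Assessor | Physiotherapist, or research assistant by telephone if the 3-month visit is missed (Outcome measures) | Treating physiotherapist, unblinded; self-report said to reduce bias |

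The efficacy sentence conflicts with the stated aim, with the design and with the Discussion's own closing paragraph.

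**2. Which outcomes are exposed.** Table 2 labels guideline attainment (by the AAQ), exacerbations, hospital admission and emergency attendance as self-reported. The CAT, mMRC and PAM are patient questionnaires. Table 2 does not say how smoking status is obtained. The primary outcomes, obstruction on spirometry and referral to pulmonary rehabilitation, are not self-reported, and process outcomes are analysed descriptively.

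**3. The plan's own numbers** (Sample size and feasibility).
- Existing COPD: 104 x 0.50 = 52, as stated. Taken as per practice, 4 x 52 = 208.
- At-risk attendees: 1060 x 0.17 = 180.2 (stated 180).
- New diagnoses: 180 x 0.18 = 32.4. The 33 printed in square brackets is read as this count.
- Largest possible follow-up group: 208 + 33 = 241. This assumes no loss to follow-up and that spirometry confirms COPD in every existing case, since only spirometry-based COPD is followed up.

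**4. How far a reporting shift alone moves the test.** The documents give no SD of change, so these are assumptions: true effect zero; mean reporting shift d = 1 CAT point (half of the 2-point minimum important difference quoted under Secondary outcomes); SD of change s = 5, 6 or 7.

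The paired t statistic is then noncentral t on n - 1 degrees of freedom, with noncentrality d x sqrt(n) / s. The rejection probability is the chance that it exceeds the two-sided 0.05 critical value in absolute size.

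| n | s | Noncentrality | P(reject) |
|---|---|---|---|
| 241 | 5 | 15.52 / 5 = 3.10 | 0.87 |
| 241 | 6 | 15.52 / 6 = 2.59 | 0.73 |
| 241 | 7 | 15.52 / 7 = 2.22 | 0.60 |
| 33 | 5 | 5.74 / 5 = 1.15 | 0.20 |
| 33 | 6 | 5.74 / 6 = 0.96 | 0.15 |
| 33 | 7 | 5.74 / 7 = 0.82 | 0.13 |

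With no shift the probability is 0.05. Any other non-causal change of the same size would have the same effect on the test.

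**The case against.** The best defence is context. The self-report sentence comes straight after an open admission that assessors are not blinded, and it promises blinded assessors later. Read there, it concerns assessor bias, and self-report does limit a rater's scoring judgement. Both sentences sit in the Discussion and change no aim, outcome, success target or analysis. The questionnaires may already be self-completed, because the protocol speaks of patients completing them. Telephone follow-up also limits missing data.

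All of this stands, and it keeps the point modest. It does not rescue the sentence as written, which speaks of bias in general, nor the efficacy claim, which the protocol contradicts elsewhere.

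A reader might infer more than the documents support:
- **That biased changes will make the cluster trial too small.** Nothing says these changes will set its effect size. Progression is tied to feasibility, and the Discussion names the qualitative results as what will modify the intervention.
- **That 180 is the sample for the paired tests.** It is the number of at-risk people expected at spirometry. Most are expected to have no COPD and will not return.
- **That ten outcomes in two columns of Table 2 mean twenty tests.** The Statistical analysis section does not say that every row is tested, or tested by cohort. Some rows are not suited to a paired t test.
- **That the research assistant should take over all 3-month assessments.** With baseline done in the physiotherapist's clinic, this would put a change of assessor into every paired difference.

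**Conclusion.** The point holds for the two claims. A single-group before-after comparison can show change but cannot test efficacy. Self-report by unblinded participants to their counselling physiotherapist narrows one kind of bias and leaves expectation and social desirability in place.

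The illustrated size is a rejection probability of 0.60 to 0.87 at 241 participants and 0.13 to 0.20 at 33, against a nominal 0.05. These figures rest on the assumed 1-point shift, SD of 5 to 7 and full follow-up; 241 also takes 52 as a per-practice figure. They show what a modest shift could do, and do not estimate the bias in this study.

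The effect of the telephone exception cannot be sized, because no expected number of missed visits is given. The primary feasibility outcomes are untouched. The correction is still worth making, since it decides what may be concluded from the 0.05 tests and costs very little.

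**What to change.** **Wording.** In the Discussion, replace the efficacy claim with feasibility wording, and speak of change in patient outcomes instead of impact. Replace the self-report clause with a statement that self-report to the treating clinician, in an unblinded and uncontrolled study, is itself a source of bias.

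**Reporting.** Give patient outcomes as change from baseline with 95% CI and SD, and make no claim of effect from p < 0.05.

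**Data collection.** Have attenders complete the questionnaires themselves before the consultation, if this is not already the practice. Report telephone-assessed participants separately, or repeat the analysis without them as a sensitivity analysis.

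**Cost.** Somewhat more modest conclusions and a little extra reporting. Self-completion needs no added staff. Recruitment began in October 2018, so any change of procedure during the study should be dated and reported; the wording and reporting changes can be made at any stage. Self-completion does not help those assessed by telephone, which is why they need separate reporting.

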## Data Availability

Data will be stored according as required by the ethics committee and will be available from the authors on request.

## Abbreviations

AAQ: Active Australia Questionnaire
ATS: American Thoracic Society
CAT: COPD Assessment Test
COPD: Chronic obstructive pulmonary disease
CDQ: COPD Diagnostic Questionnaire
ERS: European Respiratory Society
FEV_1_: Forced expiratory volume in one second
FVC: Forced vital capacity
GPs: General practitioners
GPMP: GP management plan
LABA: Long-acting beta2-agonists
LAMA: Long-acting muscarinic antagonists
LHD: Local Health District
mMRC: Modified Medical Research Council Scale for Dyspnoea
PAM: Patient Activation Measure
PASOCQ: Physical Activity Stages of Change Questionnaire
PHN: Primary Health Network
PNs: Practice nurses
PR: Pulmonary rehabilitation
RCT: Randomised controlled trial
RCTs: Randomised controlled trials
SABA: Short-acting beta2-agonists
SAMA: Short-acting muscarinic antagonists
TCA: Team care arrangement
TIDieR: Template for Intervention Description and Replication
